### Sampling method

The sampling of this part of research is carried out by available and non-probabilistic sampling method. Researcher by referring to postpartum wards of hospitals affiliated to Isfahan University of Medical Sciences on consecutive days selects 86 women with preeclampsia and having the criteria for entering the study in the easy method. Subsequently, subjects are assigned to the intervention and control groups by means of the RANDOM ALLOCATION software.

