## Abstract

**Background:**

Long-term postpartum follow-up is of great importance since women with preeclampsia history are at high risk of upcoming health complications. However, postpartum follow-up rates are poor. According to evidences, preeclampsia is not just a transient health problem; rather it causes short term and long term complications, which affect women’s life for years after delivery. Although it seems the problem is solved by the end of pregnancy, the follow-up of subjects should not be stopped after delivery. Postpartum is the best possible time to provide necessary care to these women who are at the risk of future complications. Due to importance of well-designed follow-up plan for women suffering preeclampsia, this study will carry out to provide a postpartum follow-up health care program for subjected women.

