### Sample size

With a confidence level of 95% and a statistical power of 90%, along with considering the standard deviation of lifestyle score, which is equal to P_1_ = 0.87 and P_2_ = 0.69 and with EFFECT SIZE of 0.18, the sample size is considered to be 43 in each group.

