#### Exclusion criteria

Failure to receive 50% of the intervention for any reason, having serious complications of preeclampsia, such as nephropathy and being under drug treatment, severe life stress such as spouse’s death and immigration.

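### Enrolment equals the 2 × 43 said to give 90% power, yet an exclusion rule removes intervention women after allocation, so any removal or loss takes power below the stated figure

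*Protocol article*

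**What the plan says.** Three sections of the protocol article bear on this point.

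- **Sample size.** The inputs open "With a confidence level of 95% and a statistical power of 90"%, and the result is that "the sample size is considered to be 43 in each group". No allowance for loss is mentioned.
- **Sampling method.** The researcher "selects 86 women with preeclampsia and having the criteria for entering the study in the easy method". Allocation by software to intervention or control comes after this selection. No replacement of removed women is described.
- **Exclusion criteria.** The first item is "Failure to receive 50% of the intervention for any reason". The other items are serious complications of preeclampsia and severe life stress; the article does not say whether these apply at screening, during follow-up or both.

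**The concern.** A sample-size calculation gives the number of women whose outcomes must be analysed. Here that number is also the number enrolled, and the plan has a written rule that takes women out once they have been allocated. The printed figures fit together only if nobody ever meets that rule and nobody is lost for any other reason.

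The rule also acts on one side only. A control woman has no programme to miss, so only the intervention arm can shrink through it, and the women removed are those who took up the programme least. The comparison would then be smaller than planned and would set the better attenders against all controls.

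The article's Discussion says an effective programme could enter postpartum care guidelines. A null result from a comparison with less power than advertised could be misread as lack of effect.

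**Working it through.** **Step 1. Enrolled against required.** Required: 43 per group (Sample size). Enrolled: 86 (Sampling method). 2 × 43 = 86, so the margin for loss is 86 − 86 = 0.

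**Step 2. Can the plan's 43 be reproduced?** Inputs from Sample size: 95% confidence (two-sided 5% assumed), 90% power, 0.87, 0.69 and 0.18 (= 0.87 − 0.69). With (1.960 + 1.282)² = 10.507:

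- Read as proportions, pooled formula: n = [1.960·√(2 × 0.78 × 0.22) + 1.282·√(0.87 × 0.13 + 0.69 × 0.31)]² / 0.18² = 109.2, so 110 per group.
- Read as standard deviations with a difference of 0.18: n = 10.507 × (0.87² + 0.69²) / 0.18² = 399.9, so 400 per group.
- Read as a standardised difference of 0.18: n = 2 × 10.507 / 0.18² = 648.6, so 649 per group.

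None gives 43. Read as proportions, 43 per group with no loss has power of 52% (pooled formula) to 54% (arcsine or unpooled). This is a separate fault. It is shown here because it decides what the next step may be used for.

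**Step 3. A value at which 43 would be adequate.** Solving n = 2 × 10.507 / d² for n = 43 gives d = √(21.015 / 43) = 0.699. Conversely, d = 0.70 gives n = 21.015 / 0.49 = 42.9, so 43. The plan does not state 0.70. It is used only because it grants the plan its own 43.

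**Step 4. Effect of losses.** Power is that of a two-sided 5% two-sample t-test at d = 0.70, with non-centrality d / √(1/n₁ + 1/n₂) and n₁ + n₂ − 2 degrees of freedom. The loss rates are assumed, since the article gives none.

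| Lost of 43 | Remaining | Intervention arm only (control stays at 43) | Both arms equally |
|---|---|---|---|
| 0 | 43 | 89.4% | 89.4% |
| 4 (9%) | 39 | 87.8% | 86.3% |
| 9 (21%) | 34 | 85.3% | 81.2% |
| 13 (30%) | 30 | 82.7% | 76.0% |

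The no-loss figure is 89.4% rather than 90% because the formula that returns 43 is a normal approximation. Using that approximation, calibrated so that 43 per group gives exactly 90%, intervention-only loss gives 86.1% at 34 v 43 and 83.6% at 30 v 43, and equal loss gives 82.2% and 77.3%. These are about one point higher, with the same pattern.

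**Step 5. Which column applies.** The 50% rule can produce only the intervention-only column. The equal-loss column needs ordinary dropout, or the other exclusions acting during follow-up in both arms.

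**The case against.** The strongest reply is that this is a condensed article. The full protocol may contain a loss allowance or a replacement rule, and silence about dropout would not be a finding. That is right as far as it goes, and the point does not rest on silence. It rests on three printed items that do not fit together: the required number, an identical enrolled number, and a rule that removes women after allocation.

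Several stronger readings are tempting, and the documents do not support them.

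- *Both groups will certainly be analysed with fewer than 43.* The article does not say so. The 50% rule cannot touch controls, and the timing of the other exclusions is not given.
- *The abstract predicts heavy attrition.* It does say "However, postpartum follow-up rates are poor", but this describes routine care, where the Background section says women return to primary care without a follow-up programme. It is the reason for the trial and gives no retention rate for it.
- *The loss costs 9 points or more.* That takes roughly 20% loss from both arms. For the one removal rule the plan states, about 20% loss costs about 4 points (89.4% to 85.3%).
- *Attrition explains the gap between 90% and the power implied by the printed inputs.* It does not. On the proportions reading about 36 to 38 points are missing before anyone is lost (90 less 54 or 52).
- *There is an arithmetic error in 86.* There is none; 2 × 43 is 86.

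It also stands that 0.70 is back-solved, so the power figures illustrate and do not estimate.

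**Conclusion.** The point holds in a limited form. The plan enrols exactly the number it says gives 90% power and has a rule that removes intervention women after allocation. Any such removal, or any other loss, takes the analysed number below plan and power below the stated 90%.

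The size is modest under the stated rule: about 2, 4 and 7 points for intervention-only loss of about 10%, 20% and 30%, and about 3, 8 and 13 points if both arms lose equally. These figures assume loss rates the article does not give, a two-sided 5% t-test, and a standardised difference of about 0.70 that the plan never states. The direction does not depend on those assumptions.

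This ranks below the failure of 43 to follow from the printed inputs. Correcting that calculation would not remove this point, because a new number enrolled without margin would have the same gap.

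**What to change.** 1. Delete receipt of under half of the programme as a reason for exclusion from follow-up and analysis.
2. Follow up all allocated women and analyse them in the group to which they were allocated. The 50% threshold may serve, at most, to define a secondary per-protocol analysis.
3. Restate power for the number expected to be analysed, under a loss rate that is written down as an assumption. Base it on the corrected sample-size inputs. Do not write 0.70 SD into the plan, since that would lend support to a number that the stated inputs do not yield. Inflating 43 for dropout would not help either, because it would not restore 90% power on those inputs.

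Cost: a few sentences, and a stated power that is less favourable. Women who attended little will count in the primary comparison, so the difference assumed in the power statement should allow for them. This point does not require enrolment to rise.

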#### Entry criteria

Ages ranging from 15 to 49 years, Iranian citizenship, consent to participate in the study, ability to understand questions or have reading and writing skills, not participating in simultaneous clinical trials, not having various types of severe psychiatric disorders (psychosis, schizophrenia, etc.) who are under medical treatment or in need of admission, women with preeclampsia who are nulliparous and whose delivery has led to the birth of a live newborn.

#### Exclusion criteria

Failure to receive 50% of the intervention for any reason, having serious complications of preeclampsia, such as nephropathy and being under drug treatment, severe life stress such as spouse’s death and immigration.

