### Phase III: Quantitative study

#### Type and direction of the quantitative study

The quantitative phase of the research will be implemented as a two-group semi-experimental study.

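### The 50% receipt rule excludes randomised women from the intervention arm only, and is likely to favour the programme if low attenders would score lower on lifestyle

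*Protocol article*

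**What the plan says.** Under Sampling method in the protocol article, the researcher "selects 86 women with preeclampsia and having the criteria for entering the study in the easy method". After that selection, "subjects are assigned to the intervention and control groups by means of the RANDOM ALLOCATION software". The Sample size section gives the split: "the sample size is considered to be 43 in each group". The design is labelled semi-experimental ("The quantitative phase of the research will be implemented as a two-group semi-experimental study"), but the allocation it describes is random.

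The Exclusion criteria open with "Failure to receive 50% of the intervention for any reason". The same sentence adds serious complications of preeclampsia, drug treatment, and "severe life stress such as spouse’s death and immigration". It does not say when any of these is assessed.

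The Data analysis section names t-tests, their non-parametric counterparts, tests for categorical data, and ANCOVA if confounders are present. It names no analysis set. Nothing in the article says that a woman excluded for low receipt stays in follow-up or in the analysis.

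**The concern.** An exclusion made before allocation affects both groups alike. This one cannot be made before allocation, because how much of the programme a woman receives is known only once she has been assigned to it and it has run. A control woman is offered no programme and cannot fail the rule, so her equally unengaged counterpart stays in.

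The outcome makes this matter. The questionnaire covers exercise, weight and nutrition control and disease prevention, and attending a health programme is itself a health-seeking act. Low attenders may therefore well be women who would have scored lower anyway. Removing them from one side alone can produce a difference where the programme has no effect.

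It also changes the question. The third-phase objective is the programme's effect in women with a history of preeclampsia, not in those who complete at least half of it. The Abstract describes postpartum follow-up rates as poor, and the Discussion suggests that an effective programme could enter care guidelines. Non-attendance is thus part of what the trial needs to measure.

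**Working it through.** **Step 1: order of events.** Select 86 eligible women, allocate them at random, deliver the programme, observe receipt, exclude those below 50%. The last step follows allocation and can act in one arm only. This needs no arithmetic and is enough to establish the fault.

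**Step 2: inputs for the size.**
- 43 women per arm (Sample size section).
- Fraction *f* of the intervention arm dropped: not in the documents; assumed 10% to 30%.
- Correlation *r* between receipt and lifestyle score: not in the documents; assumed 0.2 to 0.5, with 0 as a check.
- No true effect; two-sided t-test of follow-up scores at 5%.

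The figure of 43 is used here as given. It does not reproduce from the stated inputs: treating 0.87 and 0.69 as proportions, at 90% power and two-sided 5%, the usual formula gives 110 per group. That is a separate matter, and the present point does not depend on it.

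**Step 3: bias formula.** Treat receipt and lifestyle score as bivariate normal and drop the lowest fraction *f* by receipt. With z_f the *f* quantile of the standard normal and φ its density, the mean score of the retained intervention women is shifted, in SD units, by

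bias = r × φ(z_f) / (1 − f)

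- f = 10%, r = 0.2: 0.2 × 0.1755 / 0.9 = 0.039
- f = 20%, r = 0.3: 0.3 × 0.2800 / 0.8 = 0.105
- f = 30%, r = 0.5: 0.5 × 0.3477 / 0.7 = 0.248

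**Step 4: false-positive rate.** 20,000 simulated trials per setting, no true effect:

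| r | f | Mean number kept (of 43) | Bias (SD, formula) | Two-sided type I error | Significant in favour of the programme (nominal 2.5%) |
|---|---|---|---|---|---|
| 0 | 20% | 34.4 | 0 | 5.1% | 2.5% |
| 0.2 | 10% | 38.7 | 0.039 | 5.3% | 3.7% |
| 0.3 | 20% | 34.4 | 0.105 | 7.2% | 6.5% |
| 0.5 | 20% | 34.4 | 0.175 | 11.9% | 11.6% |
| 0.5 | 30% | 30.1 | 0.248 | 18.2% | 18.1% |

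With r = 0 there is no bias, so the direction rests on the correlation and not on the rule alone.

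**Step 5: sensitivity to baseline adjustment.** The paired t-tests imply a baseline measurement. Suppose ANCOVA used baseline lifestyle, with a baseline-to-follow-up correlation of 0.6 and receipt correlated equally with both. Then about (1 − 0.6) = 0.4 of the bias remains:
- r = 0.3, f = 20%: 0.4 × 0.105 = 0.04 SD
- r = 0.5, f = 30%: 0.4 × 0.248 = 0.10 SD

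Simulated two-sided type I error in these two settings is about 5.5% to 6% and 8.5%.

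**The case against.** **The analysis set may be defined elsewhere.** The article names none, and an article commonly leaves that to the full protocol or analysis plan. This would answer a complaint about missing text. The complaint here is about a rule that is stated: an exclusion criterion ordinarily means removal from the study, and this one conflicts with analysing everyone as allocated.

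**Low receipt need not mean low motivation.** The rule applies whatever the reason, which takes in illness, moving away and infant care. This stands. The direction of bias is conditional on low receivers being lower scorers. That is the natural expectation for a lifestyle outcome, but the documents do not establish it.

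**The size is assumed, and adjustment would shrink it.** This also stands. At the mild end inflation is barely visible, and adjusting for baseline lifestyle would remove much of the rest under the assumption in step 5. But the plan makes ANCOVA conditional on confounders being found and does not name baseline lifestyle as a covariate. Adjustment also cannot restore the removed women or correct for unmeasured motivation.

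**A stronger reading to resist.** A reader might infer that the other exclusions are unequal between arms too, because a follow-up programme would detect complications and start treatment more often in its own group. The documents do not support this. Those items read naturally as screening criteria, the programme's content is still to be designed in the second phase, and bereavement or immigration has no evident link to arm. All that remains is that the timing of these criteria should be stated.

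**Conclusion.** The rule is wrong as written. It removes women after randomisation, from one arm only, and forfeits the protection that the random allocation was meant to give. That conclusion rests on the text alone and is firm.

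Bias towards the programme is likely rather than certain: it requires a positive link between receipt and lifestyle score. Under the assumed range its size is about 0.04 to 0.25 SD, with a two-sided type I error of about 5% to 18% for an unadjusted comparison of follow-up scores. The upper figures need both a strong correlation and nearly a third of the arm dropped, and should not be quoted as expected values. The correction should be made before recruitment, because outcomes not collected from excluded women may be impossible to recover later.

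**What to change.** Delete the 50% receipt rule from the exclusion criteria. State that all 86 women are followed up whatever amount of the programme they receive, and that the primary analysis compares them in their allocated groups. Keep the 50% threshold only to define a secondary per-protocol analysis, labelled as such.

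As a minor clarification, state that the remaining exclusions are applied at screening, before allocation.

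The cost is protocol wording, the effort of obtaining follow-up questionnaires from women who stop attending, and possibly a smaller estimated effect. With complete outcome data, the as-allocated comparison removes this bias and returns the type I error to 5%.

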**Objectives of the third phase: quantitative study.**

Determining the effect of comprehensive postpartum follow-up health care program on the lifestyle of women with preeclampsia history.

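### Excluding women who receive less than half the programme, after random allocation and in one arm only, biases the comparison in the programme's favour

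*Protocol article*

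**What the plan says.** All references are to Phase III of the Protocol article.

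- **Design.** The section on type and direction states: "The quantitative phase of the research will be implemented as a two-group semi-experimental study".
- **Selection and allocation.** Under Sampling method, the researcher "selects 86 women with preeclampsia and having the criteria for entering the study in the easy method". The next step is: "Subsequently, subjects are assigned to the intervention and control groups by means of the RANDOM ALLOCATION software". Eligibility is therefore settled before allocation, and allocation is random.
- **Exclusion.** The first item under Exclusion criteria is "Failure to receive 50% of the intervention for any reason".
- **Outcome.** Study variables names the designed intervention as the independent variable and lifestyle as the dependent variable. Data collection method describes a 70-item interview questionnaire scored by how often a woman performs behaviours such as exercise, nutrition control and disease prevention.
- **Analysis.** Data analysis names t-tests, paired tests, rank tests and tests for categorical data, with ANCOVA only if confounders are present. No section says that excluded women stay in follow-up or in a comparison by allocated group.
- **Question.** The third-phase objective is "Determining the effect of comprehensive postpartum follow-up health care program on the lifestyle of women with preeclampsia history".

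**The concern.** Receiving half of a programme is an event after allocation. No section describes a control programme of which a woman could receive half, and applied literally to both arms the rule would exclude every control. The only workable reading is that it removes women from the programme arm alone.

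Those removed are selected on taking up health care, and the outcome is a score of health behaviours. If women who engage less with a health programme also tend to have lower lifestyle scores, removing them raises the programme arm's mean even when the programme does nothing. No matching filter applies to controls, so the protection given by random allocation is lost.

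The rule also changes the question. The Abstract's Background gives the motive for the study: "However, postpartum follow-up rates are poor". The Discussion says the programme could enter postpartum guidelines if effective. A guideline body needs the effect among women offered the programme, including those who do not take it up. The rule removes exactly those women from the study's only stated outcome.

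**Working it through.** **Inputs from the article.** 43 women per group (Sample size), random allocation (Sampling method), and a 95% confidence level, taken here as a two-sided 5% test because sidedness is not stated. The article gives no figure for expected uptake or for the bias, so there is none to reproduce on this point. The 43 itself does not follow from the stated inputs, but that is a separate matter; it is used here as the planned size.

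**Assumptions, not in the article.** The true effect is zero. A share *q* of the programme arm falls below 50% and is removed; these are the least adherent women. Adherence propensity is standard normal and has correlation *r* with the final lifestyle score.

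**Bias.** Removing the lowest *q* of a standard normal leaves a mean adherence of φ(z_q)/(1−q). The spurious difference, in SD units, is

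bias = r × φ(z_q)/(1−q)

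**Error rate.** With n₁ = round(43(1−q)) and n₂ = 43, the standard error is √(1/n₁ + 1/n₂) and the noncentrality is bias/SE. The rejection rate comes from the noncentral t with n₁ + n₂ − 2 degrees of freedom.

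**Worked case, q = 30%, r = 0.4.**
- z_q = −0.524, φ(z_q) = 0.348, and 0.348/0.70 = 0.497.
- Bias = 0.4 × 0.497 = 0.199 SD.
- n₁ = 30; SE = √(1/30 + 1/43) = 0.238; noncentrality = 0.199/0.238 = 0.835; df = 71; critical t = 1.994.
- Rejection: 13.1% two-sided, of which 12.8 points favour the programme.

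| q removed | r | n₁ vs n₂ | Spurious benefit (SD) | Two-sided error | False favourable (nominal 2.5%) |
|---|---|---|---|---|---|
| 10% | 0.2 | 39 vs 43 | 0.04 | 5.3% | 3.7% |
| 20% | 0.3 | 34 vs 43 | 0.10 | 7.4% | 6.6% |
| 30% | 0.4 | 30 vs 43 | 0.20 | 13.1% | 12.8% |
| 40% | 0.5 | 26 vs 43 | 0.32 | 24.8% | 24.7% |

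**Check by simulation.** A separate null simulation of 40,000 trials per setting gave +0.11 SD and 7.8% two-sided error at q = 20%, r = 0.3, and +0.31 SD and 25.0% at q = 40%, r = 0.5. At r = 0 there was no bias for any q.

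**All women analysed as allocated.** With 43 against 43, simulated two-sided error was 4.8–4.9% and bias was essentially zero at every correlation tried (0 to 0.5).

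**Scale.** By the t-test, 43 per arm has 90% power at a true difference of about 0.71 SD. The spurious 0.20 SD in the third row is about 28% of that (0.20/0.71).

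**The case against.** The strongest case against is about size.

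1. **Baseline adjustment.** The figures above compare unadjusted final scores. Paired tests imply a baseline measurement, and ANCOVA is available. If adherence reflects a stable trait, it shows in the baseline score too. Assuming equal correlation of adherence with baseline and final score, and a baseline–final correlation of 0.6 (not in the article), simulated two-sided error under ANCOVA falls to about 6%, 7% and 10% in the last three rows of the table, with bias of about 0.04, 0.08 and 0.13 SD. A change-score comparison has roughly nominal error. This stands as a limit on size, but it does not rescue the rule. ANCOVA is conditional, no between-group comparison of change is named, and adherence that predicts change itself would bias every one of these analyses.

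2. **Unknown inputs.** Neither *q* nor *r* is given, and the mildest case is close to nominal. The rule also covers non-receipt for logistic reasons, which need not relate to lifestyle; taking all those removed as the least adherent is unfavourable to the plan. This stands: the direction is well supported, the size is not known.

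3. **Inferred premises.** The article does not say what controls receive, and the programme is yet to be designed, so how it will be delivered is unknown. Other exclusions, such as serious complications and severe life stress, could remove women from either arm. This is fair, but none of it puts an adherence filter on controls.

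4. **Condensed article.** A fuller document might add an analysis by allocated group. The point, however, is not a missing analysis set. The article states a removal rule under its exclusion criteria, and a fuller document could neutralise it only by departing from that text.

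**Conclusion.** The concern holds. As written, the rule removes women after random allocation, on uptake, from one arm only, in a study whose sole outcome is a health-behaviour score. Whenever uptake and lifestyle are positively related, the bias favours the programme.

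Under the stated assumptions, the chance of a false favourable result from unadjusted final scores runs from 3.7% (10% removed, correlation 0.2) to 24.7% (40% removed, correlation 0.5), against 2.5%. Baseline ANCOVA would more than halve the bias if adherence is a stable trait and the baseline–final correlation is near 0.6. If uptake and lifestyle are unrelated there is no bias, but the article gives no ground for relying on that. This should be corrected before the comparison is made.

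**What to change.** - Delete the clause on receiving 50% of the intervention from the exclusion criteria.
- State that every allocated woman is asked for the final lifestyle interview, including those who stopped taking part, and is analysed in her allocated group whatever share of the programme she received.
- Report the share received as a process result.
- If a result among women with at least 50% exposure is wanted, present it as a labelled secondary analysis that does not decide effectiveness.

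**Cost.** A sentence or two in the protocol and a few extra interviews, with no additional participants. The estimated effect will probably be somewhat smaller, because women who did not take up the programme now count. If telephone interviews are used to reach women who stopped attending, offer them in both arms and record the mode, so that mode of data collection does not differ mainly in one arm.
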